Patient blood management is an evidence-based, patient-tailored approach aimed at reducing the need for ABT and its associated risks [18]. Patient blood management has both preoperative and perioperative components. Preoperative techniques include patient optimization via cessation of antiplatelet and anticoagulant medications [19,20] and anemia management [18]. Perioperative management comprises achieving surgical hemostasis, reinfusion of intraoperatively salvaged blood, the use of erythropoietic agents, and hemostatic drugs such as tranexamic acid. Randomized [21,22] and nonrandomized [23] studies on the use of IOCS in nononcological surgical procedures indicate that salvaged blood transfusion (SBT) significantly reduces the need for ABT [21-23]. Despite extensive use of SBT in orthopedic, trauma, and cardiac surgical procedures [24], the concern of reinfusion of tumor cells leading to disease progression persists [25-27]. The initial lack of literary evidence on the safety of SBT in oncological surgical procedures has made oncological surgeons reluctant to use SBT in MSTS [25-27].

This reluctance dates to an American Medical Council report from 1986, which stated that SBT was not suitable for use in tumor surgery [28]. This was in turn based on a case report from 1975 where tumor cells were found in salvaged blood [29]. There were concerns that tumor manipulation and resection would result in the spillage of tumor cells into the surgical field [30], which would lead to further metastasis if reinfused via SBT. Recent evidence indicates that circulating tumor cells (CTCs), which are shed by the primary tumor [31], are the most likely cause of tumor metastasis in oncological patients. CTCs have been shown to be eliminated by the reticular endothelial system [32], once they fail to metastasize (unable to complete the process of metastasis). Other CTCs may undergo cellular apoptosis after being retained in the capillary bed or the bone marrow [32]. These host defense mechanisms can prevent metastasis by reducing the metastatic ability of the vast majority of CTCs [33]. Consequently, one can ask, “Can SBT with a limited load of damaged malignant tumor cells cause tumor metastasis and disease progression?”

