#### Secondary Objectives

The secondary objectives of the study are to investigate whether reinfusion of IOCS-LDF–processed blood can reduce ABT rates in patients undergoing MSTS. We will also compare the length of stay and overall complication rate of patients who receive salvaged blood and those who receive ABT or no blood transfusion (NBT).

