## Methods

### Recruitment

This study aims to recruit a minimum of 90 patients of whom 30 will receive SBT (with or with no allogeneic blood), 30 will undergo ABT, and the remaining 30 will have NBT. From our experience of treating patients with tumor, there are likely to be very few patients who receive only SBT. The majority of patients receiving SBT are likely to receive both SBT and ABT in various proportions. SBT and ABT form the 2 experimental arms, whereas patients with NBT form the control cohort. We will compare the number of patients receiving only SBT with those receiving ABT, if the sample sizes are sufficient.

Patients will be selected from specialist outpatient spine clinics or inpatient wards. These patients may be referred from an inpatient medical oncology team for management, especially in the setting of MSD with cord compression resulting in symptoms such as pain or neurology. A thorough examination of clinical history, physical examination, and review of imaging will be done, and appropriate patient management options will be discussed by the attending orthopedic surgeon. During the enrollment period, whenever a spine surgeon has obtained surgical consent for MSTS in patients with MSD, the principal investigator (NK) will be informed either by a telephone call or by text messaging.

The *research assistant* who is on-site at the National University Hospital during office hours or any member of the research team who is available will interview the patient. During this interview, the interviewer will confirm whether the inclusion criteria are fully met. The study will be explained to suitable subjects, including the advantages as well as possible intra- and postoperative risks of the reinfusion of salvaged blood. A copy of the *patient information sheet and consent form* will be provided to the patient, detailing the recruitment procedures, our objectives, hypotheses, and background information, and any queries will be addressed. Subsequently, written informed consent will be obtained from the patient.

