Blood transfusion details will be collected from anesthetists immediately after the operation. Depending on the type of blood transfusion done during the surgery, that is, ABT only or SBT with or with no ABT or NBT, the patient will be categorized into the appropriate study cohort. All patients undergoing MSTS will receive tranexamic acid as an intravenous bolus before induction of anesthesia as per the department protocol, with subsequent top-up dosages every 4 hours during MSTS. If excessive blood loss is expected during surgery, such as in a separation surgery, continuous infusion of tranexamic acid is given to the patient.

Postoperatively, all subjects will be followed up individually by their operating surgeons, as per the standard of care at the National University Hospital. No additional patient follow-up sessions by the research team will be required. Clinical data and patient outcomes will be accessed via the computerized patient support system and EPIC system at monthly intervals. All available radiological data and clinical notes from the patients’ follow-up by their treating surgeons or physicians will be reviewed by the research team. This is to determine the postoperative outcomes such as survival and disease progression. The collected data will be analyzed postoperatively at 3, 6, 12, 24, 36, and 48 months. The data collection and follow-up of available records will continue over a period of 4 years postoperatively or until the patient’s demise, whichever occurs first. The collected outcomes of the 2 experimental groups (patients who received SBT with or without ABT) will be compared with those of the control group (patients who received NBT) as well as with the available historical data from the literature.

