#### Analysis of Primary Outcome Measures

We intend to compare the proportion of patients with MSTS requiring blood transfusion and the amount of ABT required. The primary analysis will be based on the intention-to-treat principle. A Fisher exact test will be used to compare the 2 arms. The exact 95% CI will also be calculated for the difference in the ABT rate between the 2 arms.

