### Broader Implications

Through the reporting of our analysis, this study will help reduce the use of ABT, reduce the burden on blood banks, and improve the overall blood management of patients with MSTS. This improvement in blood management will prevail even with the improvement of surgical techniques in the management of MSTS, that is, introduction of minimally invasive surgery techniques and the regular use of navigation. This is because the 2 techniques mentioned earlier will reduce blood loss during the steps of spinal instrumentation but are unlikely to have any effect on blood loss while performing decompression. Decompression and separation surgery presently still form a major component of MSTS and will continue to do so, resulting in significant bleeding that requires replenishment potentially in the form of SBT.

In this protocol, we have proposed a prospective observational nonrandomized study design as the ethical appropriateness of blinding or randomizing these patients is a key concern in our region and country. Blinding or randomization of patients with MSD could be deemed unethical, especially among patients who may not agree to receive SBT or ABT as this will limit the blood transfusion type applicable for them. This could be attributed to the current lack of clinical evidence that SBT does not lead to disease progression or shortened survival among patients undergoing MSTS who receive SBT. With this research proposal, we aim to highlight the safety profile of SBT, together with a design protocol applicable for use in patients with MSD. Future research, such as propensity-matched studies, can be done to further validate the outcomes from our current protocol.

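### The ABT comparison is unadjusted in a nonrandomized study, although expected blood loss drives ABT need and also sets the tranexamic acid regimen

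*Protocol article*

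**What the plan says.** The ABT question is stated under Secondary Objectives: to "investigate whether reinfusion of IOCS-LDF–processed blood can reduce ABT rates in patients undergoing MSTS". Its analysis appears under Analysis of Primary Outcome Measures, which covers the proportion transfused and the amount of ABT. For the rate, "A Fisher exact test will be used to compare the 2 arms", with an exact 95% interval for the difference. That section names no test for the amount. The general Statistical Analysis section offers one-way ANOVA or Kruskal-Wallis for continuous variables.

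On tranexamic acid, Recruitment says: "All patients undergoing MSTS will receive tranexamic acid as an intravenous bolus before induction of anesthesia as per the department protocol", with top-ups every 4 hours, and then: "If excessive blood loss is expected during surgery, such as in a separation surgery, continuous infusion of tranexamic acid is given to the patient". Background lists, as parts of perioperative management within an approach meant to reduce ABT, "reinfusion of intraoperatively salvaged blood, the use of erythropoietic agents, and hemostatic drugs such as tranexamic acid".

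On allocation, Broader Implications says "we have proposed a prospective observational nonrandomized study design". Recruitment fills the cohorts postoperatively: "Depending on the type of blood transfusion done during the surgery, that is, ABT only or SBT with or with no ABT or NBT". By contrast, the Objective in the Abstract sorts patients by whether they consent to salvaged blood, and Analysis of Primary Outcome Measures invokes intention-to-treat.

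**The concern.** Expected bleeding is a plain candidate confounder of the ABT comparison. It drives the need for ABT: Background links a typical loss of about 1500 mL to an average of 3 units. It also determines which tranexamic acid regimen is used, so the regimen is a marker of expected bleeding as well as a treatment with its own possible effect on ABT. Nothing in the design balances either of them between arms.

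The article provides multivariable models for overall survival and for tumor progression, but none for ABT. It mentions propensity matching only for heterogeneity of primary tumors (Limitations) and for future research (Broader Implications). If the arms turn out to differ in expected bleeding or regimen, the stated ABT analysis has no means of separating that from an effect of salvaged blood. At stake is the claim that salvage reduces ABT.

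**Working it through.** **Plan's own figure.** The minimum of 90 patients (30 per cohort) comes without an effect size, event rate or power, so it cannot be reproduced. It is not disputed here; 30 per arm is used below as the planned size.

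**Inputs.** From the article: 30 per arm, two-sided 5% level, Fisher exact test, 3 units as average need. Assumed, because the article gives none of them: the share of each arm on infusion, the ABT risk with and without infusion, and the ratio of ABT need between regimens.

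**ABT rate, true salvage effect set to zero.** Rate in an arm = s × r(inf) + (1 − s) × r(no), where s is the infusion share and r the ABT risk. The spurious difference (SBT, salvaged blood, minus comparator) is therefore [s(SBT) − s(comparator)] × [r(inf) − r(no)]. Fisher rejection was obtained by exact enumeration at 30 v 30.

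| r(no) v r(inf) | Shares 50/50 | 60/40 | 70/30 | 80/20 |
|---|---|---|---|---|
| 50% v 60% | 0 points, 2.7% | 2, 2.9% | 4, 3.4% | 6, 4.4% |
| 40% v 70% | 0 points, 2.7% | 6, 4.4% | 12, 10.1% | 18, 20.9% |
| 30% v 80% | 0 points, 2.7% | 10, 7.7% | 20, 25.7% | 30, 56.1% |

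Each cell gives the spurious difference, then the rejection rate. Example: (0.70 − 0.30) × (0.70 − 0.40) = 0.12. The sign turns if the infusion stratum has the lower ABT risk: 60% v 50% with shares 80/20 gives (0.80 − 0.20) × (0.50 − 0.60) = −6 points.

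**ABT amount.** Spurious difference = share gap × (ratio − 1) × 3 units, where the ratio is ABT need under infusion relative to no infusion.

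- Gap 0.4, ratio 0.7: 0.4 × (−0.3) × 3 = −0.36 units, or 12% of 3 units, in favor of salvage.
- Gap 0.4, ratios 0.6 to 1.4: −0.48 to +0.48 units.

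The 3 units are an overall average in Background. Using them as the no-infusion baseline is a further assumption.

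**Rate under as-treated cohorts.** Recruitment names SBT and ABT as the two experimental arms and fills them by the blood given. Every patient in the ABT-only cohort then has ABT, so that arm is 30/30. Fisher against 25/30 in the SBT arm gives p = 0.052, and against 24/30 p = 0.024, whatever the regimen. Stratifying does not help, because the ABT-only rate is 100% in every stratum. The table therefore applies only if arms are set by consent or intention.

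**The case against.** The strongest reply is that no section says infusion use differs between arms. The tranexamic acid rule follows expected bleeding and makes no reference to arm, and the Abstract suggests that consent decides who gets salvaged blood. With balanced use the bias is zero. This stands. A reader might infer that a tranexamic acid effect is already being counted as a salvage effect, or that the ABT difference cannot be attributed to salvage at all. The documents support neither: they show an unprotected comparison, not a demonstrated bias, and even its direction is open.

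A second reply is that covariates are commonly left to the statistical analysis plan, and that tranexamic acid regimen is one candidate among several. This stands in part. A list of covariates is not owed here, and for the amount the ABT section fixes no test. For the rate, however, the protocol does fix a method, and that method is unadjusted, while the survival and progression analyses are given adjusted models.

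A third reply is that a yes/no regimen variable captures expected bleeding only coarsely. This also stands. Adjustment reduces confounding but leaves variation in bleeding within each regimen. Nor are two regimens in themselves an error.

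**Conclusion.** The point holds as a conditional one. In a nonrandomized study, the ABT rate comparison is fixed as a crude Fisher test with a crude interval, and the tests on offer for ABT amount are crude as well, although a variable tied to ABT need and known before transfusion is there to be recorded. If the arms differ in expected bleeding or regimen, the estimated salvage effect is distorted by an amount and in a direction that the article does not allow one to state.

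The assumed ranges run from no distortion to 30 points on the rate, and to about half a unit either way on the amount at a 40-point share gap. With weak strata (50% v 60%), Fisher rejection stays at or below 4.4%. These figures show what is possible, not what is expected. For the rate, the point depends on arms set by consent or intention. Under as-treated cohorts the 100% ABT-only rate is a separate and larger obstacle. A revision is advisable, with medium confidence.

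**What to change.** In Analysis of Primary Outcome Measures:

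- Record tranexamic acid regimen and surgery type (for example, separation surgery) for every patient, and report both by arm.
- **ABT amount:** make the main comparison a regression of ABT units on arm, regimen and surgery type. Both covariates must be taken as determined before surgery, not revised in the light of observed bleeding.
- **ABT rate:** give a risk difference with 95% interval, stratified by or adjusted for the same variables. Define arms by consent or intention to use salvaged blood, and count all patients in them, including those who end up without transfusion. Ethical Considerations reads as if every recruit consents to salvaged blood, so the text must state which preoperative record sets the arm.
- Keep the crude Fisher test and exact interval as supportive.

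The cost is analysis wording plus two variables. Anesthetists already supply transfusion details after each operation, so the regimen could be collected at the same point. Intervals will be somewhat wider, strata may be sparse at about 30 per arm, and confounding within regimen will remain and should be acknowledged. How tranexamic acid is given is left as it is.

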### Statistical Analysis

We have defined *disease progression* as the increase in the size of an existing metastatic lesion or the appearance of a new lesion in the lung, liver, or the spinal column, which can be visualized by using radiological imaging.

Demographic and clinical characteristics of patients will be summarized using mean (SD) values for continuous variables with approximately normal distribution, median (IQR) values for continuous variables with skewed distribution, and frequency (percentage) for categorical variables. A 1-way ANOVA will be used to compare the mean of a normally distributed variable across the 3 blood transfusion groups, whereas a Kruskal-Wallis rank test will be used for the comparison of medians. A Fisher exact test will be implemented for categorical variables accounting for potential small frequencies.

The association between individual characteristics and OS will be studied by using the Kaplan-Meier curve and a log-rank test. The crude hazard ratio and its 95% CI will be used to measure the association between individual characteristics and OS and will be calculated based on their original definitions. Multivariate Cox proportional hazard regression will then be used to adjust for statistically significant confounders for the relationship between the type of blood transfusion and OS. The proportional hazards assumption will be tested after the final model is obtained.

The association between the type of blood transfusion and tumor progression will be investigated by the competing risks analysis, taking death without tumor progression as the competing event. First, cumulative incidence curves of the 3 blood transfusion groups will be plotted nonparametrically, and then we will model the relation via a subdistribution hazard regression model. The measure of association will be quantified by the crude subdistribution hazard ratio; its 95% CI and *P* value will be analyzed in a univariate analysis. Subsequently, a multivariate analysis will be used to adjust for potential confounders. All statistical analyses will be done using Stata Special Edition 14.0 (StataCorp LP). The statistical tests will be assumed to be 2-sided, with the conventional 5% significance level.

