### Objectives

#### Primary Objectives

This study aims to investigate the following clinical outcomes: disease progression, in terms of tumor progression (increase in size of existing metastatic lesions with or without the appearance of new metastasis), and the overall survival (OS) in patients who receive *IOCS in combination with LDF* (IOCS-LDF)–processed blood during MSTS. Therefore, this study aims to refute the prevailing conception that cell salvage should be avoided in MSTS owing to concerns of tumor dissemination.

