#### Analysis of Secondary Outcome Measures

The progression of disease will be assessed using the internationally accepted Response Evaluation Criteria in Solid Tumors (version 1.1) [66,67]. Disease progression is defined as at least a 20% increase in the sum of the diameters of measurable target lesions (eg, lymph nodes and bone metastases with soft tissue components), unequivocal progression of nontarget lesions (eg, malignant ascites or pleural effusions), or the appearance of 1 or more new metastatic lesions.

Computed tomography of chest or abdomen and pelvis will be used to assess metastases in the lymph nodes, lung, liver, or any abdominal organ, all of which can be visualized adequately. Magnetic resonance imaging of whole spine and nuclear medicine bone will also be performed because of their increased sensitivity in detecting early new spinal or skeletal metastases [68]. A lesion identified in a follow-up study in an anatomical location that is not present at baseline is considered a new lesion and will indicate disease progression.

The OS rate will be defined as the proportion of patients who survive until the end of the study period. Median survival times and 95% CI will be estimated using Kaplan-Meier curves for experimental and control groups. The median OS times will be compared using a log-rank test. The survival rate at 6 months after surgery will also be estimated using Kaplan-Meier curves.

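### The Methods define disease progression in two conflicting ways, and the competing-risks analysis is not tied to the RECIST 1.1 definition

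*Protocol article*

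**What the plan says.** All references are to the protocol article.

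- **Statistical Analysis** gives an explicit definition of disease progression: growth of "an existing metastatic lesion or the appearance of a new lesion in the lung, liver, or the spinal column", provided it can be seen on imaging. It sets no size threshold and names three sites for new lesions. The same section holds the only regression planned for progression, a subdistribution hazard model "taking death without tumor progression as the competing event".
- **Analysis of Secondary Outcome Measures** says progression will be assessed by RECIST 1.1 and gives a second explicit definition: "Disease progression is defined as at least a 20% increase in the sum of the diameters of measurable target lesions", unequivocal progression of non-target lesions, "or the appearance of 1 or more new metastatic lesions". It adds: "A lesion identified in a follow-up study in an anatomical location that is not present at baseline is considered a new lesion". The imaging it lists covers lymph nodes, abdominal organs and the skeleton as well as lung, liver and spine.
- **Primary Objectives** and **Hypothesis** gloss tumor progression in parentheses as "increase in size of existing metastatic lesions with or without the appearance of new metastasis".

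The article does not present either Methods definition as a summary of the other, and it does not say which one supplies the events for the model.

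**The concern.** Tumor progression is half of the primary objective and of the safety hypothesis; the other half is overall survival. If the event is defined in two ways, the same records can give two different event counts and two different hazard ratios.

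The study hopes to find no increase in risk, so the direction of any error matters. A rule with no threshold admits events that reflect measurement variation only. A rule limited to three sites leaves out spread elsewhere, and spread is the harm feared from reinfusing salvaged blood. The study is also non-randomized and unblinded (Broader Implications), and the research team determines progression from routine records (Recruitment). An open definition therefore leaves room to choose after outcomes have been seen.

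**Working it through.** The article states no progression rate, event target or power for progression, so there is no figure to reproduce. The check has two parts.

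**1. The same patients under both Methods definitions.** The cases are constructed for the check. The rules are those of the two sections.

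- Rule A (Statistical Analysis): event if the size change is above 0, or if there is a new lesion in lung, liver or spinal column.
- Rule B (Analysis of Secondary Outcome Measures): event if the change in summed target diameters is at least 20%, or if there is a new lesion at any site. Non-target progression is not exercised in these cases.

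| Case | Rule A | Rule B |
|---|---|---|
| Target sum 50 to 55 mm (5/50 = +10%), no new lesion | event | no event |
| Target sum 50 to 60 mm (10/50 = +20%), no new lesion | event | event |
| New lung lesion only | event | event |
| New lymph-node or femur lesion only | no event | event |
| +10% and a new femur lesion | event | event |

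The first and fourth cases disagree in opposite directions. Neither rule contains the other, so rule A cannot be a shorthand for rule B.

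**2. What the missing threshold does in a stable patient (illustration).** Assumptions, none of them from the article: the true size does not change; the baseline and follow-up measurements are each 1 + c·Z, with Z independent standard normal; c is 5% or 10%; any numerical excess over baseline counts as growth under rule A.

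- Any increase: P(follow-up > baseline) = 0.50 by symmetry, whatever the value of c.
- The 20% rule: P(follow-up ≥ 1.2 × baseline). The quantity follow-up − 1.2 × baseline has mean 1 − 1.2 = −0.2 and SD c·√(1 + 1.2²) = 1.562c.
  - c = 0.10: z = 0.2/0.1562 = 1.28, probability about 0.10.
  - c = 0.05: z = 0.2/0.0781 = 2.56, probability about 0.005.

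At one scan, then, 50% of stable patients would be labelled progressed under rule A, and about 0.5% to 10% under rule B. The probability that at least one scan crosses the line rises with the number of scans under either rule. The article gives analysis times but no scan schedule, so only the single-scan figure is used here.

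**Direction.** False events that occur at the same rate in every group carry no information about the transfusion type. Added to the true events, they pull the hazard ratio towards 1.

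**The case against.** The best defence is that the RECIST paragraph is the operational rule and the sentence in Statistical Analysis a general description. The RECIST paragraph has the threshold, the imaging and the new-lesion rule; the other sentence has no measurement rule. This is a plausible account of what was intended, and it supports keeping RECIST. It does not remove the conflict. The general sentence is worded as the study's definition, names sites that RECIST does not limit, and stands directly above the model.

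The illustration can also be challenged, and fairly. The error sizes are assumed. The Statistical Analysis wording requires growth that is visible on imaging, so a reader of scans would not call every numerical excess an increase, and the 50% may be too high in practice.

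Two stronger readings are tempting, and the documents support neither.

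- *That there are three incompatible definitions, one of which excludes new metastasis alone.* Read literally, the wording in Primary Objectives and Hypothesis does exclude it. But it is a parenthetical gloss that no analysis uses. Both Methods definitions count a new lesion alone (the first within its three sites), and Study Findings in the Discussion describes progression as either new metastasis or growth of the index lesion. This is loose drafting.
- *That most events under the no-threshold rule would be measurement noise.* The calculation covers only truly stable patients. If a fraction s of patients is stable and every true progressor is labelled, noise is the majority at one scan only when 0.5s > 1 − s, that is, s > 2/3. The article gives no value for s.

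The analysis sections also place progression under secondary outcomes although the objectives make it primary. That is a separate inconsistency and does not settle which definition applies.

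**Conclusion.** The point holds as a contradiction between two explicit Methods definitions of an endpoint in the primary objective. It is not detail left to a fuller document, because no further document can make both definitions true. The classification in part 1 rests on the article's wording alone and needs no assumption.

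The size is illustrative: 50% of stable patients falsely labelled at one scan without a threshold, against about 0.5% to 10% with the 20% rule, for independent error of 5% to 10%. The pull of the hazard ratio towards 1 assumes that false events are equally frequent in all groups. The loss of dissemination events outside lung, liver and spinal column follows directly from the site limit; its frequency cannot be derived from the article.

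This should be settled before progression is analyzed, since as written the endpoint cannot be counted reproducibly.

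**What to change.** 1. Use the RECIST 1.1 definition in Analysis of Secondary Outcome Measures, with new lesions at any site, throughout.
2. Delete the definition that opens Statistical Analysis.
3. State there that the cumulative incidence curves and the subdistribution hazard model use the RECIST 1.1 event.
4. As a wording note, make the gloss in Primary Objectives and Hypothesis read *and/or* new metastasis, in line with Study Findings.
5. Optionally, report time to first new metastatic lesion as a component, because it is closest to the dissemination concern. Resolving the contradiction does not require it.

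The cost is wording; the optional component uses the same scans. There will be fewer size-based events than under a rule counting any increase, partly offset by new lesions at sites now excluded.
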